# SCHEDULE OF ASSESSMENT

| **Phase (duration)** | **0** | **I** | | **II** | | | | | | **Follow-Up** | | **Unscheduled**  **Visit** |
| --- | --- | --- | --- | --- | --- | --- | --- | --- | --- | --- | --- | --- |
|  | max. 1 week | Initial ECT series  (max. 6 weeks and max. 18 ECTs are allowed) | | 28 weeks | | | | | | 12 months | |  |
| **Visit** | **Screening/ inclusion** | **1** | **2** | **2a** | **2b** | **2c** | **2d** | **2e** | **3** | **4a** | **4b** |  |
| **Time** | Before start of stabilization*  (max. 7 days before visit 1) | 1-2 day(s) before the first ECT | 1 day after last ECT (week 0) | 3rd calendar week ** or  on the day of the 3rd mECT | 6^th^ calendar week after V2 or  on the day of the 6th mECT | 10^th^ calendar week after V2 or on the day of the 8th mECT | 14^th^ calendar week after V2 or on the day of the 10th mECT | 19^th^ calendar week after V2 or on the day of the 12th mECT | 28^th^ calendar week after V2  or on the day of the last mECT | 6 mo. after visit 3 | 12 mo. after visit 3 |  |
| Informed Consent | **x** |  |  |  |  |  |  |  |  |  |  |  |
| In-/Exclusion Criteria | **x** |  |  |  |  |  |  |  |  |  |  |  |
| Sociodemographics^1^ |  | **x** |  |  |  |  |  |  |  |  |  |  |
| Medical History |  | **x** |  |  |  |  |  |  |  |  |  |  |
| Concomitant Medication / Therapy |  | **x** | **x** | **x** | **x** | **x** | **x** | **x** | **x** | **x** | **x** | **x** |
| Vital Signs^2^ |  | **x** |  |  |  |  |  |  | **x** |  | **x** | **x** |
| Randomization^3^ |  |  | **x** |  |  |  |  |  |  |  |  |  |
| Adverse events |  |  |  | **x** | **x** | **x** | **x** | **x** | **x** | **x** | **x** | **x** |
| **Intervention** |  |  |  |  |  |  |  |  |  |  |  |  |
| TAU or mECT + TAU |  |  |  | **x**^4^ | **x**^4^ | **x**^4^ | **x**^4^ | **x**^4^ | **x**^4^ | **x**^5^ | **x**^5^ |  |
| **Questionnaires/tests** |  |  |  |  |  |  |  |  |  |  |  |  |
| Brief Psychiatric Rating Scale |  | **x** | **x** | **x** | **x** | **x** | **x** | **x** | **X** | **x** | **x** | **x** |
| Global Assessment of Functioning |  | **x** | **x** | **x** | **x** | **x** | **x** | **x** | **x** | **x** | **x** | **x** |
| Positive and Negative Symptom Scale |  | **x** | **x** | **x** | **x** | **x** | **x** | **x** | **x** | **x** | **x** | **x** |
| Hamilton Rating Scale for Depression |  | **x** | **x** | **x** | **x** | **x** | **x** | **x** | **x** | **x** | **x** | **x** |

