| Mini Mental State^6^ Examination |  | **x** | **x** | **x** | **x** | **x** | **x** | **x** | **x** | **x** | **x** | **x** |
| THINC-it ®^6^ |  | **x** | **x** | **x** | **x** | **x** | **x** | **x** | **x** | **x** | **x** | **x** |
| Northoff Catatonia Rating Scale (German version) |  | **x** | **x** |  |  |  |  |  | **x** | **x** | **x** | **x** |
| Q-LES-Q-18 |  | **x** | **x** |  |  |  |  |  | **x** | **x** | **x** | **x** |
| Self-Stigma of Mental Illness Scale – Short Form |  | **x** | **x** |  |  |  |  |  | **x** | **x** | **x** | **x** |
| Stigma-Stress-Scale |  | **x** | **x** |  |  |  |  |  | **x** | **x** | **x** | **x** |

ECT: Electroconvulsive Therapy; mECT: Maintenance Electroconvulsive Therapy; TAU: treatment as usual; THINC-it: THINC integrative tool; Q-LES-Q-18: Abbreviated Quality of Life Enjoyment and Satisfaction Questionnaire

*Stabilization: implementation of any major medication changes before the initiation of the ECT series

** The times indicated as weeks refer to the TAU group, however the respective mECT should be scheduled within the respective week. Visit 2 is regarded to take place in week 0, e.g. calendar week 20. For the patients receiving mECT, the first mECT should be scheduled in the next calendar week, e.g. calendar week 21, and the 3^rd^ mECT (Visit 2a) should take place in calendar week 3 after V2, e.g. calendar week 23. A calendar week is from Monday to Sunday. Two mECTs cannot be performed in the same calendar week

^1^ Sociodemographics: Age, sex, education, marital status, residence

^2^ Vital signs: height, weight

^3^ All baseline characteristics (including vital signs, medical history, prior medication, …) must be assessed **before** randomization. Randomization should be carried out only in subjects with improvement of 30% or more on the Brief Psychiatric Rating Scale (BPRS).

^4^ According to randomization

^5^ Treatment depending on patients’ choice

^6^ Mini-Mental State Examination (MMSE) and Thinc-it must be performed before mECT is administered.

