## Risk Benefit Assessment

All procedures performed during this study are routine clinical procedures and are mentioned within German guidelines. Of course, all side effects will be recorded. Severe side effects are not expected (27), since they are known to be extremely rare (and not study related).

The most common side effect in phase one will be cognitive side effects due to ECT. These will be monitored not only by MMSE, but also by THINC-it and by clinical observation. THINC-it has been validated multiple times in the past (28), especially for treatment-related changes of cognitive function in both depression (29) and schizophrenia (30). Of course, this monitoring will continue in phase two as well, although significant differences between groups are not expected to occur during this phase. Typically, cognitive side effects after an acute ECT series subside after about 15 days (31). There is no evidence for further decline of cognitive function with maintenance ECT (32), but evidence of further improvement.

Participants might personally benefit from study participation due to closer and more standardized monitoring compared to routine clinical practice. Future patients with clozapine-resistant schizophrenia will benefit from the study results, as they will most likely lead to a change in guidelines for treatment-resistant schizophrenia.

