## Secondary Objectives and Endpoints

The secondary objectives are to compare side effect profile and safety as well as psychopathological changes between mECT plus TAU versus TAU only.

The secondary endpoint for treatment efficacy is the proportion of relapse free subjects at the end of phase II.

Further secondary endpoints are:

- BPRS
- Global assessment of functioning (GAF) allowing a general (34) and PANSS allowing a differentiated view on specific symptom dimensions (35)
- HAMD (36) monitoring depression, since ECT and mECT have a well-known positive influence on mood
- The Northoff catatonia rating scale (NCRS-dv) (37) assessing the full spectrum of catatonic symptoms
- Q-LES-Q-18, an abbreviated and validated Quality of Life Enjoyment and Satisfaction Questionnaire for subjects with schizophrenia (38)
- The Self-Stigma of Mental Illness Scale – Short Form (SSMIS-SF) (39) and the Stigma-Stress-Skala (40) are used for self-labeling and stigma
- MMSE (41) and THINC-it (28-30) monitoring cognition

All secondary endpoints listed above are analyzed at the end of phase II and at the end of follow-up.

Safety will be also determined by the frequency of adverse events from randomization up to the last follow-up visit.

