# Study Design

This is a German multi-center, observer-blind, randomized, and actively controlled parallel-group study to compare after a successful series of routine electroconvulsive therapy (ECT) the overall effectiveness of maintenance ECT (mECT) plus treatment as usual (TAU) versus TAU only in subjects aged from 18 to 65 years with the indication of clozapine resistant schizophrenia.

A schematic of the study design is shown below:

[figure not shown]

**Phase I:** Subjects will be included in the study according to the inclusion and exclusion criteria and will receive an ECT series with a maximum of 18 ECT treatments based on a clinical indication for ECT or until there is a clinically sufficient response to treatment.

**Phase II:** Subjects who respond to ECT in phase I (BPRS score < 70% of BPRS at visit 1) meet the inclusion criteria for phase II of the study. After completing the ECT series in phase I and before starting phase II, subjects are randomized to receive either maintenance ECT plus standard treatment or standard treatment alone.

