# Subject Selection

## Number of Subjects and Sites

A total of 140 subjects will be enrolled in the study (phase I) and 84 subjects will be randomized (phase II), i.e. 42 subjects per treatment group (see chapter 9.9).

The study will be national and multicenter.

It is intended that the study will take place at approximately 14 German sites.

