## Characteristics of Adverse Events

- - 1. Grading of AEs

The grading of AEs in this study will be carried out on the basis of the 5-grade scale defined in the CTCAE V 5.0:

| Grade 1: | Mild; asymptomatic or mild symptoms; clinical or diagnostic observations only; intervention not indicated. |
| --- | --- |
| Grade 2: | Moderate; minimal, local or non-invasive intervention indicated; limiting age-appropriate instrumental Activities of Daily Living (ADL)*. |
| Grade 3: | Severe or medically significant but not immediately life-threatening; hospitalization or prolongation of hospitalization indicated; disabling; limiting self-care ADL**. |
| Grade 4: | Life threatening consequences; urgent intervention indicated. |
| Grade 5: | Death related to AE. |

*Instrumental ADL refer to preparing meals, shopping for groceries or clothes, using the telephone, managing money, etc.

**Self-care ADL refer to bathing, dressing and undressing, feeding self, using the toilet, taking medications, and not bedridden.

The grading of all AEs listed in the CTCAE v 5.0 will be based on the information contained therein. The grading of all other AEs, i.e., those which are not listed in the CTCAE v 5.0 will be performed by a responsible investigator, based on definitions given above.

If an AE shows an undulating course of intensity, it must be documented only once with predominant or medically most appropriate intensity / with the highest intensity grade.

- - 1. Causal Relatedness

The investigator will evaluate each AE that occurred after randomization regarding the **relatedness** with the study intervention:

| Related | There is a reasonable possibility of a causal relatedness between the event and the study intervention, i.e. the possibility for a causal relatedness between the study intervention and the AE cannot be excluded. |
| --- | --- |
| Not related | There is no reasonable possibility of a causal relatedness between the AE and the study intervention, i.e. there is a clear alternative explanation. |

- - 1. Outcome of AEs

All subjects who have reportable AEs, whether considered associated with the use of the study intervention or not, must be monitored to determine the outcome. The clinical course of the AE will be followed up until resolution or normalization of changed laboratory parameters or until it has changed to a stable condition. This also holds for ongoing AEs/SAEs of withdrawn subjects.

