## Period of Observation and Documentation

Adverse events (AEs) will be ascertained by the investigators using non-leading questions, noted as spontaneously reported by the subjects to the medical staff at any time during the study or observed at any of the study visit.

The observation period begins with randomization and ends with the last study visit.

AEs with a grading ≥ 2 will be documented in the subject file and in the CRF. AEs of grade 1 will not be documented in the subject file and in the CRF. If applicable, all medical diagnoses or symptoms occurring prior to the beginning of the period of observation and documentation will be recorded in the CRF as medical history.

The following general rules apply to the documentation of the AEs and SAEs: The start date of an SAE must not be earlier than that of the corresponding AE. The end date of a SAE is typically the same as that of AE. The end date of the SAE must not be later than the end date of the corresponding AE. AEs and SAEs that are ongoing at the time of death are considered not resolved or resolving.

All SAEs and their relevance for the benefit-risk assessment of the study will be evaluated continuously during the study and for the final report. All SAEs will be documented in the CRF.

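### Adverse event recording opens only at randomisation, so the phase I ECT series specified for all 140 enrolled subjects yields no AE or SAE records, although section 1.3 says side effects are recorded

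*Protocol*

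**What the plan says.** Four places in the protocol set the start of AE recording, and they agree.

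- Section 8.3: "The observation period begins with randomization and ends with the last study visit".
- Section 2.2: "Safety will be also determined by the frequency of adverse events from randomization up to the last follow-up visit".
- Section 8.2.2 asks for a relatedness judgement on "each AE that occurred after randomization".
- The AE row of the schedule is empty at screening, visit 1 and visit 2. Its first mark is at visit 2a.

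The schedule times visit 2 as "1 day after last ECT (week 0"), and section 6 places randomisation at the end of that visit. The whole phase I series therefore lies before the window.

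Phase I is part of the study. Section 4.1 states: "A total of 140 subjects will be enrolled in the study (phase I) and 84 subjects will be randomized (phase II"). Section 5.1, under the study intervention, sets electrode placement, dose, anaesthetic and a cap of 18 sessions for it. Section 3 describes the series as given "based on a clinical indication for ECT or until there is a clinically sufficient response to treatment".

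Section 8.3 sends earlier diagnoses and symptoms to medical history where applicable, and leaves grade 1 AEs out of the file and the CRF. Section 1.3 says of the study as a whole: "Of course, all side effects will be recorded".

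**The concern.** Section 1.3 gives a general assurance about side effects and then turns directly to those expected in phase one. Read in order, the assurance covers phase I. The operative rules in sections 2.2, 8.2.2 and 8.3 do not.

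What is at stake is safety oversight:

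- Section 8.3 calls for continuous review of SAEs for the benefit-risk assessment.
- Section 12.5 asks the DSMB to evaluate tolerability, and gives public doubt about the safety of ECT as one reason for having a board.
- Section 7.4 allows the study to stop if the benefit-risk balance comes into doubt.

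None of these can draw on phase I AEs that were not recorded. Section 9.5 also plans an exploratory model in all recruited subjects to find who is likely to benefit from the first ECT course. Benefit would be examined in 140 subjects, and AEs would exist only for those randomised.

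**Working it through.** **1. Subjects outside the window.** Inputs: 84 to be randomised and 60% entering phase II (section 9.9).

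- Required enrolment: 84 / 0.60 = 140, which reproduces the protocol's figure.
- Not randomised: 140 − 84 = 56, and 56 / 140 = 40%.
- The 56 is a planning figure. It includes responders unwilling to continue as well as non-responders.

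**2. Order of events (schedule, sections 5.1 and 6).**

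- Consent at screening.
- Visit 1, one to two days before the first ECT. This is the only visit with a medical-history mark.
- Phase I: at most 18 sessions at three per week, so 18 / 3 = 6 weeks.
- Visit 2, one day after the last ECT, with randomisation at its end. The AE window opens here.
- Visit 2a in week 3: first AE mark.

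**3. ECT exposure on either side of the window's start.** Before it: up to 18 sessions per subject, for all 140. After it: 6 + 5 + 4 = 15 scheduled maintenance sessions, for the 42 in that arm.

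**4. What could still capture a phase I event.**

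- *Cognitive tests.* MMSE and THINC-it are done at visits 1 and 2. They cover cognition, not anaesthetic, cardiovascular or other medical events, or a prolonged hospital stay, which section 8.1.2 counts as serious.
- *Medical history.* Footnote 3 of the schedule ("All baseline characteristics (including vital signs, medical history, prior medication" and so on) places these items before randomisation, so an update at visit 2 is possible for randomised subjects. It would carry no grade, seriousness or relatedness, and the footnote does not help subjects who are never randomised.
- *Wider wording.* Section 6.2 has AEs asked about whenever investigator and subject meet. Section 6 wants the visit 3 assessments, which include AEs, if participation ends early. Section 8.3 itself says every SAE goes into the CRF. None of these is limited to randomised subjects, yet all sit beside an explicit window that is.

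**5. Effect of opening the window at the first phase I ECT.** Planned AE coverage rises from 84 to 140 subjects (+56). Sample size, power and the primary analysis do not change.

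**The case against.** The best defence is that the window is a deliberate and consistent choice. Safety is a secondary objective framed as a comparison of the two arms, and counting from randomisation suits that comparison. Phase I is clinically indicated, on-label routine ECT, and the experimental treatment begins only after randomisation. The assurance in section 1.3 is one general sentence that does not promise graded AE forms, and rewording it would remove that contradiction.

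Part of this stands. The window is right for the between-arm comparison, and routine status justifies lighter recording in phase I. It does not justify none: section 1.3 calls all study procedures routine, maintenance ECT included, yet AEs under maintenance ECT are recorded. Rewording section 1.3 alone would leave SAEs in consented, protocol-specified treatment outside the record, and sites would still face the conflicting wording in sections 6, 6.2 and 8.3.

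Three stronger readings are tempting but not supported:

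- *The arm comparison is biased.* It is not. Both arms pass through phase I before randomisation and share the same window.
- *The 56 subjects have no provision for AEs anywhere.* That is too absolute. They fall outside the section 8.3 period, but the wider wording could be read to reach them. The text is in conflict, not silent.
- *A known majority of ECT sessions, and so of events, is lost.* With every subject at the cap and full maintenance adherence, the share would be (140 × 18) / (140 × 18 + 42 × 15) = 2,520 / 3,150 = 80%. But section 3 stops the series at sufficient response, section 7.2 stops maintenance ECT at relapse or withdrawal, and the protocol gives no mean number of phase I sessions. The actual share cannot be derived, and sessions are exposure, not events.

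**Conclusion.** The point holds as a matter of safety-data collection. Under sections 2.2, 8.2.2 and 8.3 and the schedule, AEs and SAEs during the phase I ECT series are not recorded with grade, seriousness and relatedness. Up to 18 sessions per subject precede recording, and a planned 56 of 140 subjects (40%) never enter the observation period. This conflicts with section 1.3, as does the exclusion of grade 1 AEs.

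The size rests on the protocol's own 60% entry rate and session cap; the number of unrecorded events cannot be estimated from the document. No estimand, error rate or power figure is touched. The consequence for the DSMB follows from the window, since the protocol does not say which data its two safety analyses will contain. The change is worth making because it is cheap and because uncollected data cannot be recovered at the analysis stage.

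**What to change.** Amend the protocol as follows.

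- **Section 8.3:** document all SAEs and AEs of grade 3 or higher from the first phase I ECT to randomisation or, for subjects not randomised, to visit 2 or the last phase I contact. From randomisation on, keep grade 2 or higher plus all SAEs. Limit the medical-history sentence to events before the first ECT.
- **Section 8.2.2:** extend the relatedness judgement to these phase I events.
- **Schedule:** add an AE mark at visit 2. For early stops in phase I, use the existing unscheduled-visit column or the last ECT contact, since no early-stop visit is defined.
- **Section 9.5:** list phase I events descriptively, apart from the randomised comparison, which keeps its start at randomisation as in section 2.2.
- **Section 1.3:** state what is recorded, including that grade 1 AEs are not.

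The cost is an amendment and modest extra site documentation. Subjects with a reportable phase I event also need follow-up to resolution or stability (section 8.2.3) and MedDRA coding (section 10.2). Phase I events have no control group and must be presented as descriptive only.

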## Assessments

- **Sociodemographic:** Age, sex, marital status, education (in years including: school degree (Hochschulreife/Abitur, Realschulabschluss, Hauptschulabschluss), university degree (bachelor), higher education (master, PhD)) and residence (city with 100.000 inhabitants, town with 10.000 inhabitants and rural area)
- **Medical history:**

This includes psychiatric history including number of psychotic episodes, prior treatments and concomitant psychiatric disorders, other clinically significant diseases, surgeries, previous medical procedures, smoking history, use of alcohol and other drugs, and all current medications (e.g., prescription drugs, over-the-counter drugs, herbal or homeopathic remedies, and nutritional supplements).

- **Vital signs/physical examination:** Height, weight
- **Concomitant medication:** Medication taken during subject’s enrollment will be documented.
- **AEs:**

AEs will be asked for at each contact between the responsible investigator and the subject. AEs will be reported with subject ID, start and end date, description, grading, seriousness, relatedness, action taken and outcome.

- Treatment (mECT) parameters (see section 5.1)

The following **questionnaires** will be completed by the investigator during the study visits:

- **Brief Psychiatric Rating scale (BPRS):** A 18-item rating scale to measure psychiatric symptoms such as depression, anxiety, hallucinations and unusual behavior using a seven-item Likert scale. The BPRS will be assessed by means of a clinical interview that will be recorded on video and rated by a blinded rater and unblinded raters at the sites.
- **Global Assessment of Functioning (GAF):** A numeric scale to rate the social, occupational, and psychological functioning of an individual. Scores range from 100 (extremely high functioning) to 1 (severely impaired).
- **Positive and Negative Syndrome Scale (PANSS):** A numeric scale used for measuring symptom severity of patients with schizophrenia. The subject is rated from 1 to 7 on 30 different symptoms. The total score ranges from 30 to 210.
- **Mini Mental State Examination (MMSE):** The examination will be performed to screen for cognitive impairment and associated reduction. It includes tests of orientation, attention, memory, language and visual-spatial skills. The patient can reach a maximum of 30 points (no cognitive impairments) in MMSE total score.

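### The protocol promises and analyses all adverse events but bars grade 1 events from both records, and its unresolved rule for undulating events lets the site decide whether some events enter the data

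*Protocol*

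**What the plan says.** Section 1.3 (Risk Benefit Assessment) tells the reader: "Of course, all side effects will be recorded".

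Section 2.2 makes safety a comparison between arms: "The secondary objectives are to compare side effect profile and safety as well as psychopathological changes between mECT plus TAU versus TAU only". It then names the measure: "Safety will be also determined by the frequency of adverse events from randomization up to the last follow-up visit". Section 9.5 plans to tabulate the subjects with one or more adverse events by MedDRA term. Neither section mentions a grade.

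Section 6.2 has adverse events asked about at every contact and adds: "AEs will be reported with subject ID, start and end date, description, grading, seriousness, relatedness, action taken and outcome". No threshold is given there either.

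Section 8.3 sets one: "AEs with a grading ≥ 2 will be documented in the subject file and in the CRF". The next sentence closes the door on the rest: "AEs of grade 1 will not be documented in the subject file and in the CRF". The same section sends all serious adverse events to the CRF.

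Section 8.2.1 says of an event whose intensity goes up and down that "it must be documented only once with predominant or medically most appropriate intensity / with the highest intensity grade".

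**The concern.** There are two separate defects, and they interact.

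The first is a contradiction about what is captured. A reader of sections 1.3, 2.2 and 9.5 expects the safety tables to cover every adverse event after randomization. Under section 8.3 they cannot. A subject whose only events were grade 1 will be tabulated as having had none. A threshold for CRF entry is a common economy. Keeping grade 1 events out of the subject's own file goes further, because it removes the evidence on which the threshold was applied.

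The second is the grading rule for undulating events. It offers two different answers and no way to choose. Normally that would blur only the recorded grade. Combined with a threshold at grade 2, it can decide whether there is a record at all. Section 3.4.2 accepts that the observer at the site cannot be blinded, so the choice falls to staff who know the arm.

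At stake is a listed secondary objective, the comparison of side effect profile and safety. It also bears on the material for the DSMB, which under section 12.5 meets twice to look at tolerability.

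**Working it through.** The documents give no adverse event rates and no figure to reproduce, so the check is a comparison of text followed by a case-by-case application of the rules.

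**Step 1: what is counted against what is captured.**

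| Section | Scope stated |
| --- | --- |
| 1.3 | every side effect recorded |
| 2.2 | frequency of adverse events, no grade limit |
| 6.2 | adverse events reported with grading, no grade limit |
| 9.5 | subjects with one or more adverse events, no grade limit |
| 8.3 | grade 2 or higher in file and CRF; grade 1 in neither; all serious events in CRF |

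A mild side effect after randomization is a grade 1 adverse event under section 8.2.1. Section 1.3 requires it to be recorded and section 8.3 forbids it, so both cannot be followed. The data available for sections 2.2 and 9.5 are those that section 8.3 lets through: grade 2 or higher, plus any serious event.

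**Step 2: can the threshold be verified?** Under section 13.2 the monitor reviews CRF entries and source documents. If no event appears in either place, two histories fit: nothing happened, or something happened and was graded 1. With the subject file closed to grade 1, they cannot be told apart.

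**Step 3: apply both undulating rules, then the threshold.** Rule A grades by the prevailing intensity. Rule B grades by the peak.

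| Course of the event | Rule A | Rule B | Consequence |
| --- | --- | --- | --- |
| mostly grade 1, peak grade 2 | grade 1, no record | grade 2, recorded | presence in the data differs |
| mostly grade 1, peak grade 3, not serious | grade 1, no record | grade 3, recorded | presence in the data differs |
| mostly grade 1, peak meets a seriousness criterion | in CRF as serious | in CRF as serious | presence does not differ |
| mostly grade 2, peak grade 3 | grade 2, recorded | grade 3, recorded | only the grade differs |

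The first half of the rule also allows the medically most fitting intensity, which may equal either A or B and so adds discretion. In the first two rows the choice also decides whether a subject with no other event counts in the section 9.5 table.

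**Step 4: exposure.** Section 5.1 schedules 6 + 5 + 4 = 15 mECT sessions. With 42 subjects in the mECT arm (section 4.1) the ceiling is 42 × 15 = 630 sessions in phase II. This is an upper limit on sessions, not a count of lost events.

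**The case against.** The best defence is that a grade 2 threshold is an explicit choice, applied alike to both arms, in a trial of routine, on-label procedures with risk-based quality management. By the protocol's own definitions grade 1 needs no intervention, and grade 2 begins where even minimal intervention is indicated, so what is dropped is mild. That is a fair argument for limiting CRF entry. It does not reconcile sections 1.3, 2.2 and 9.5 with section 8.3, does not justify the bar on source entry, and does not resolve the slash in section 8.2.1.

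The defence does dispose of several stronger readings that a reader might infer:

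- *Common ECT side effects disappear from the trial.* The protocol nowhere says that these are mostly grade 1. The one it calls most common, and that for phase I, is cognitive. Cognition is measured by MMSE and THINC-it at every visit from visit 1 on and summarised by group whatever the adverse event grade.
- *The filter removes harms from the mECT arm alone.* Observation starts at randomization, at visit 2, one day after the last acute ECT, so residual effects can occur in both arms. In follow-up, mECT is by patient choice whatever the randomized arm. More mild session-related events in the mECT arm during phase II are plausible, but the documents do not show it.
- *Events that worsen from grade 1 lose their onset.* Section 6.2 asks for a start date once an event is reported, and nothing stops the true onset being entered. Only a contemporaneous note would be missing.
- *The loss spans 630 sessions.* Relapse and withdrawal end the intervention, and section 9.9 plans for a 61.5% event rate in that arm, so fewer sessions are to be expected.
- *Effects that recur after each session are all undulating events.* If they resolve between sessions they could equally be separate events.

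**Conclusion.** The point stands as an inconsistency that changes which events are counted. As written, the adverse event comparison describes grade 2 or higher (plus serious events of any grade), while the endpoint and analysis are worded as if they covered all events. The boundary between grades 1 and 2 is not verifiable from source. For a non-serious event that is mostly grade 1 with a higher peak, the choice between the rules in section 8.2.1 decides whether it is in the data.

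The size cannot be stated: no event rates are given, and the share of undulating events that cross the boundary is unknown. The direction of any bias between arms is also not established. The primary endpoint, sample size and power are untouched, since adverse event grades do not enter the relapse definition.

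The conclusion rests on reading section 8.3 literally, as a bar on both records. A statistical analysis plan, not shown here, could restrict the tables to grade 2 or higher, but it could not recover events that were never written down or settle how a site graded them.

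**What to change.** 1. In section 8.2.1 keep one rule: an undulating event is documented once, at its highest grade. State that the grade 2 threshold applies to that grade.
2. In section 8.3 delete the bar on entering grade 1 events in the subject file, so that the threshold decision can be checked.
3. If the CRF threshold of grade 2 is kept, restate the safety endpoint in section 2.2 and the safety analysis in section 9.5 as adverse events of grade 2 or higher, mention serious events of any grade, and correct section 1.3 to match.

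Entering grade 1 events in the CRF as well would be an alternative to item 3. That is a trade-off between data entry and completeness, and the point does not depend on it.

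The cost is a short amendment and slightly more source documentation, with no added visits. The trial would also have to accept a narrower stated safety claim, which is the one its data can support.
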